### Data collection and patient outcomes

In this prospective longitudinal study, data will be acquired from burns patients at the following 19 postinjury time points: days 1–14, day 28 (±3 days) and months 3, 6, 12 and 24 (±2 weeks). Patient enrolment into the study began on 27 November 2016, with an estimated end date of December 2025.

Across the settings of paediatric and adult burns, a significant number of studies have undertaken serial blood sampling to investigate the short (<1–7 days), medium (8–34 days) and long (35–1100 days)-term inflammatory response to thermal injury and its relationship with patient outcome.^22–28^ In contrast, very little data currently exist on the acute and long-term effects of thermal injury on the immune system.^19 24 29^ Thus, generating data on the kinetics of the immune response to burn injury via serial sampling in both our adult and paediatric cohorts will allow us to not only establish how long burn-induced changes in immunity persist for, when compared with HCs, but also compare the immune response of septic and non-septic burns patients over time. Generating and interrogating such novel data may provide mechanistic insights into the long-term health complications reported by survivors of burn trauma, which include an increased susceptibility to respiratory infections.^30^

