#### Exclusion

Associated multiple injuries with an injury severity score (ISS) >25.Decision not to treat due to the severity of the injury. This decision will be made at the time of hospital admission.Patients with chemical or deep electrical burns.Patients receiving glucocorticoid treatment.Patients with active malignancy.Patients with multiple limb amputations (amputations would skew the calculation of TBSA scores).Patients with known long-term infections (eg, hepatitis B and C, HIV).

Alongside burns patients, a maximum of 100 adults and 10 children will be recruited to serve as a cohort of age-matched healthy controls (HCs), with the only exclusion criterion being current treatment with anti-coagulant medication or an acute infection.

Adult HCs can be recruited from age 16 years, with no upper age limit. Enrolment of up to 100 healthy adults will enable us to undertake diverse sampling of the adult population, allowing us to control for as many of the variations that encompass this broad age range as possible (eg, general physical condition, concurrent medical conditions and drug therapies, past exposure to disease or injury and different degrees of physiological ageing). Adult HC volunteers will be recruited through advertisements disseminated at the QEHB, BCH, the University of Birmingham campus and via online newsletters. When an expression of interest for study participation is received by the burns research team, a patient information leaflet (PIL) detailing the conditions of the study will be sent to the volunteer. All subjects who receive a PIL will be recorded on a screening log that will be held in the site file at the QEHB. Adult volunteers will attend the QEHB to participate in the study.

The paediatric HC group will consist of children undergoing elective plastic surgery procedures at the BCH. These surgeries will include mole removal, correction of prominent ears, revision of plastic surgery and cosmetic type surgery. In terms of age range and a lack of other health conditions or ongoing medical treatments, paediatric HCs will represent a more homogeneous cohort when compared with our adult HC group. Thus, we expect to observe much less variability in the baseline immune profiles of paediatric HCs. This factor, combined with the complexity of recruiting paediatric HCs, is the reasoning behind our decision to enrol a maximum of 10 healthy paediatric volunteers into the SIFTI-2 study.

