#### Demographic and physiological data

Within 24 hours of injury, information on patient demographics, injury characteristics and baseline physiological data will be collected and recorded in paper and electronic CRFs. At subsequent study time points, physiological data will be collected and recorded in the electronic CRF. Table 1 summarises the data that will be recorded for all patients.

**Table 1 T1:** Demographic and clinical data that will be recorded in patient case report forms following enrolment into the SIFTI-2 study

Day 1 (within 24 hours of injury)			Days 2–14	Day 28, months 3, 6, 12, 24
Demographic data	Injury characteristics	Physiological data	Physiological data	Physiological data
Age Sex Ethnicity Time from injury to arrival at burn centre Medical comorbidities History of alcohol or substance misuse	% TBSA % Body surface area full thickness burn Burn mechanism Presence of inhalation injury and severity ABSI APACHE II AIS ISS NISS PIMS-2 Revised Baux score GCS score	Heart rate (bpm) Blood pressure (mm Hg) Mean arterial pressure (mm Hg) Oxygen saturation (%) Respiratory rate (breaths/minute) Temperature (^o^C) Blood glucose (mMol/L) Height (m) Weight (kg) BMI (kg/m^2^)	Heart rate (bpm) Blood pressure (mm Hg) Mean arterial pressure (mm Hg) Oxygen saturation (%) Respiratory rate (breaths/minute) Temperature (^o^C) Blood glucose (mMol/L) Height (m) Weight (kg) BMI (kg/m^2^) Mode of ventilation Early Warning Score Use of haemofiltration or dialysis Date of discharge/Date of death	Heart rate (bpm) Blood pressure (mm Hg) Mean arterial pressure (mm Hg) Oxygen saturation (%) Respiratory rate (breaths/minute) Temperature (^o^C) Blood glucose (mMol/L) Height (m) Weight (kg) BMI (kg/m^2^)

PIMS-2 scores will be calculated for children<16 years. % TBSA will be calculated using the Lund and Browder chart.

ABSI, Abbreviated Burn Severity Index; AIS, Abbreviated Injury Scale; BMI, body mass index; GCS, Glasgow Coma Scale; APACHE II, Acute Physiology And Chronic Health Evaluation II; ISS, Injury Severity Score; NISS, New Injury Severity Score; PIMS-2, Paediatric Index of Mortality Score-2; SIFTI-2, Scientific Investigation of the Biological Pathways Following Thermal Injury-2; TBSA, total body surface area.

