### Data analysis

Data will be assessed for normality using the Shapiro-Wilk test. Normally distributed data will be presented as mean values with SD. Non-normally distributed data will be presented as median values with IQR. Comparisons of baseline continuous data (eg, demographics, injury characteristics) between two groups (eg, HCs vs burns patients or septic vs non-septic patients) will be conducted using an unpaired Student’s t-test for normally distributed data or the Mann-Whitney U test for non-normally distributed data. Categorical baseline data will be compared using a χ^2^ test. Laboratory data obtained from HCs and patients across the different sampling time points will be compared using either a one-way analysis of variance with a Dunnett post hoc test for normally distributed data or a Kruskal-Wallis test with a Dunns post hoc test for non-normally distributed data. A p <0.05 will be considered statistically significant.

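### Controls with an acute infection are excluded, but no matching rule is stated for patients' late samples, so an intercurrent infection can be read as a persisting burn effect

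*Protocol article*

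**What the plan says.** The Exclusion section sets the rule for healthy controls (HCs): they are recruited "with the only exclusion criterion being current treatment with anti-coagulant medication or an acute infection". For patients, the only infection criterion is applied at entry and concerns chronic disease: "Patients with known long-term infections (eg, hepatitis B and C, HIV". No section says that a patient's later sample is postponed, excluded or marked because of an acute infection.

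Data collection and patient outcomes sets 19 sampling times, of which the late ones are day 28 and months 3, 6, 12 and 24. The stated use of the series is to "establish how long burn-induced changes in immunity persist for, when compared with HCs", and also to compare septic with non-septic patients over time. The same paragraph names, among the long-term complications reported by survivors, "an increased susceptibility to respiratory infections".

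Under Demographic and physiological data, the article states: "Table 1 summarises the data that will be recorded for all patients". The column headed "Day 28, months 3, 6, 12, 24" lists vital signs, glucose, height, weight and BMI. The Outcomes section separately has burn wound infection or sepsis entered in the CRF, without a time limit.

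Data analysis fixes the comparison: "Laboratory data obtained from HCs and patients across the different sampling time points will be compared using either a one-way analysis of variance" with Dunnett's test, or Kruskal-Wallis with Dunn's test. Neither an infection term nor a restriction on samples is given.

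**The concern.** Acute infection is treated as disqualifying for a reference sample but not for the patient sample set against it. The two groups therefore differ by design in something other than the burn, and the resulting difference is to be described as burn-induced. The article itself gives a reason to expect the imbalance: it reports that survivors are more prone to respiratory infection.

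At stake is the claim about how long immune changes last. If some patients at a late visit have a current infection, and if it moves the immature granulocyte count, phagocytic capacity or cfDNA, part of the late difference from controls is a transient response. A lasting alteration and a response to a current illness are different conclusions, and the comparison as stated cannot tell them apart. The late septic versus non-septic comparison could be affected too, if infection rates at follow-up differ between those groups.

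**Working it through.** The article gives no figure for infection at follow-up, so there is nothing of its own to reproduce here. The calculation shows what would follow under stated assumptions.

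**Inputs from the article.** Up to 100 adult controls (Exclusion); 19 patient sampling times (Data collection and patient outcomes); Dunnett's test against controls, p<0.05 (Data analysis).

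**Assumed inputs.** 100 patients at a visit; no true residual burn effect; marker SD of 1 in uninfected people; a share f of visits with an infection; each infection shifts the marker by s SD; no infections among controls.

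**Step 1, bias.** The mean shift in patients is f × s. With s = 2:
- f = 5%: 0.05 × 2 = 0.10 SD
- f = 10%: 0.10 × 2 = 0.20 SD
- f = 15%: 0.15 × 2 = 0.30 SD
- f = 20%: 0.20 × 2 = 0.40 SD

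**Step 2, standard error.** The patient variance is 1 + f(1 − f)s². For f = 10% and s = 2 this is 1 + 0.09 × 4 = 1.36. The standard error of the difference is √((1 + 1.36)/100) = 0.154, and the expected test statistic is 0.20/0.154 = 1.30. For f = 5%, 15% and 20% the expected statistics are 0.68, 1.89 and 2.46.

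**Step 3, critical value.** For 19 comparisons with one control group of equal size, the two-sided 5% Dunnett value is about 2.89 (large samples). The nominal error of a single comparison is then 2 × (1 − Φ(2.89)) = 0.4%.

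**Step 4, false-positive rate per visit.** This is Φ(expected statistic − critical value), plus a negligible opposite tail. For f = 10%: Φ(1.30 − 2.89) = Φ(−1.59) = 5.6%.

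| Visits with infection (s = 2) | Mean shift | Planned Dunnett test, 2.89 | Unadjusted test, 1.96 |
|---|---|---|---|
| 5% | 0.10 SD | 1.4% | 10% |
| 10% | 0.20 SD | 5.6% | 26% |
| 15% | 0.30 SD | 16% | 47% |
| 20% | 0.40 SD | 33% | 69% |

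The last column is shown only because it is the figure one gets by overlooking the planned multiplicity correction.

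**Step 5, sensitivity to the assumptions.** With s = 1, the Dunnett figures for 5%, 10%, 15% and 20% are 0.6%, 1.4%, 3.1% and 6.3%. With 2% of visits infected and s = 2, the shift is 0.04 SD and the rate is 0.5%, in effect the nominal level. On the rank-based route, a simulated rank test at 0.05/19, as a stand-in for Dunn's test, gave about 0.7%, 2.7%, 7.7% and 16% at s = 2. The correction lowers the false-positive rate but leaves the bias in Step 1 as it is.

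**The case against.** The strongest reply is that the article does not show infection to be unrecorded. A reader might infer from Table 1 that it is, but the table only summarises, and it sits under a heading on demographic and physiological data. Its column for days 2 to 14 also leaves out platelets, insulin, cultures and feeding, all of which the Outcomes section needs for diagnosing sepsis. Burn wound infection or sepsis is stated to go into the CRF. This stands: absence from the table does not prove absence from the CRF, and the full protocol may hold more. What remains is the rule that is stated: an exclusion on one side of the comparison only.

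A reader might also infer that the three markers were chosen because they respond to infection. The article says otherwise: they were chosen because day 1 values discriminated patients who later developed sepsis. That a minor infection at month 6 or 12 shifts them is an assumption.

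Third, infection after a burn may be a consequence of the burn. Removing infected samples could then remove the patients with the most persistent dysfunction. This also stands. It argues against making a persistence claim depend on the analysis without those samples, but not against showing both.

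Finally, temperature, heart rate and respiratory rate are recorded at late visits and could serve as a crude screen. No such use is stated.

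**Conclusion.** The point holds as a minor weakness in a secondary aim. Acute infection is removed from the controls and not from the patients' day 28 and month 3 to 24 samples, while the late difference is attributed to the burn. An intercurrent infection can therefore be read as persistence.

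How much this matters cannot be settled from the article. Under the assumptions above, the bias is 0.1 to 0.4 SD and the false-positive rate per visit about 1% to 33% when 5% to 20% of visits carry an infection worth 2 SD. It is negligible if infections are rare, and smaller if the shift is smaller. False-positive rates of 26% or more at 10% infected, which an unadjusted test would suggest, do not apply to the planned Dunnett comparison. Nor does the article support saying that late differences are infection artefacts; it supports only that they could be.

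The day 1 prediction of sepsis, the model built on it and the sample size of 245 are unaffected.

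**What to change.** At each day 28 and month 3 to 24 sample, flag whether the patient has an acute infection and whether antibiotics are in use. For visits already made, take this from the clinic record. If the CRF already holds these items, say so and name them. Report the comparison with controls twice, once with all samples and once without the flagged ones. Interpret any difference between the two with the stated caveat that infection may itself follow from the burn.

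The cost is one CRF item, some retrospective record checking, one repeat analysis and slightly fewer samples in that repeat. No extra patients or blood are needed, and no sample-size figure changes.

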#### Demographic and physiological data

Within 24 hours of injury, information on patient demographics, injury characteristics and baseline physiological data will be collected and recorded in paper and electronic CRFs. At subsequent study time points, physiological data will be collected and recorded in the electronic CRF. Table 1 summarises the data that will be recorded for all patients.

**Table 1 T1:** Demographic and clinical data that will be recorded in patient case report forms following enrolment into the SIFTI-2 study

Day 1 (within 24 hours of injury)			Days 2–14	Day 28, months 3, 6, 12, 24
Demographic data	Injury characteristics	Physiological data	Physiological data	Physiological data
Age Sex Ethnicity Time from injury to arrival at burn centre Medical comorbidities History of alcohol or substance misuse	% TBSA % Body surface area full thickness burn Burn mechanism Presence of inhalation injury and severity ABSI APACHE II AIS ISS NISS PIMS-2 Revised Baux score GCS score	Heart rate (bpm) Blood pressure (mm Hg) Mean arterial pressure (mm Hg) Oxygen saturation (%) Respiratory rate (breaths/minute) Temperature (^o^C) Blood glucose (mMol/L) Height (m) Weight (kg) BMI (kg/m^2^)	Heart rate (bpm) Blood pressure (mm Hg) Mean arterial pressure (mm Hg) Oxygen saturation (%) Respiratory rate (breaths/minute) Temperature (^o^C) Blood glucose (mMol/L) Height (m) Weight (kg) BMI (kg/m^2^) Mode of ventilation Early Warning Score Use of haemofiltration or dialysis Date of discharge/Date of death	Heart rate (bpm) Blood pressure (mm Hg) Mean arterial pressure (mm Hg) Oxygen saturation (%) Respiratory rate (breaths/minute) Temperature (^o^C) Blood glucose (mMol/L) Height (m) Weight (kg) BMI (kg/m^2^)

PIMS-2 scores will be calculated for children<16 years. % TBSA will be calculated using the Lund and Browder chart.

ABSI, Abbreviated Burn Severity Index; AIS, Abbreviated Injury Scale; BMI, body mass index; GCS, Glasgow Coma Scale; APACHE II, Acute Physiology And Chronic Health Evaluation II; ISS, Injury Severity Score; NISS, New Injury Severity Score; PIMS-2, Paediatric Index of Mortality Score-2; SIFTI-2, Scientific Investigation of the Biological Pathways Following Thermal Injury-2; TBSA, total body surface area.

For adult HCs, the following clinical information will be recorded: date of birth, gender, weight in kilograms, height in metres and smoking status (active, ex-smoker or never smoked). The same details in addition to information relating to past medical history/congenital anomaly history will be recorded for paediatric HCs.

#### Blood sampling

The schedule for blood sampling of adult and paediatric burns patients and the blood volumes that will be obtained are outlined in figure 2. For children, the volume of blood that will be acquired on days 1, 3, 5, 7, 10, 12, 14 and 28 as well as months 3, 6, 12 and 24 postburn will be dependent on their weight (table 2). For adult burns patients treated with low molecular weight heparin, blood samples on study days 5, 10 and 14 will be obtained 3 hours post-treatment. Blood samples will be taken following local standard operating procedures either from an arterial or central venous line or via venepuncture. The source of the blood samples will be dependent on the type of intravenous access the patient has. Posthospital discharge, research follow-up visits will take place during the patient’s clinical follow-up appointments where possible. For HCs, 9 and 18 mL blood samples will be acquired from paediatric and adult volunteers, respectively, by venepuncture.

**Figure 2 F2:**
[figure not shown]
Blood sampling schedule for paediatric and adult burns patients. For children, the volume of blood that will be acquired on days 1, 3, 5, 7, 10, 12, 14 and 28 as well as months 3, 6, 12 and 24 postburn will be dependent on their weight.

**Table 2 T2:** Blood volumes to be obtained from thermally injured children (<16 years) enrolled into the SIFTI-2 study

Age range	Weight range	Maximum blood volume that can be taken over 30 days*	Days 2, 4, 6, 8, 9, 11, 13	Days 1, 3, 5, 7, 10, 12, 14, 28, months 3, 6, 12, 24
			Blood volume to be taken	Blood volume to be taken
1–5 years	10–18 kg	40–72 mL	2 mL	3.25 mL
5–7 years	19–29 kg	76–116 mL	2 mL	7.75 mL
8–12 years	30–40 kg	120–160 mL	2 mL	13.25 mL
12–15 years	>40 kg	>160 mL	2 mL	18.25 mL

*The maximum blood volume that can be taken for research over a 30-day period is 5% of a patients total blood volume (TBV). The TBV of a child is around 75–80 mL/kg.

SIFTI-2, Scientific Investigation of the Biological Pathways Following Thermal Injury-2.

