#### Inclusion

Patients aged 1–15 years admitted with a ≥20% TBSA burn.Patients aged 16 years and over admitted with a≥15% TBSA burn.

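### Table 2's paediatric draw schedule uses the whole 5% blood allowance at the lower edge of each weight band at 80 mL/kg, so the cap fails there at the footnote's own 75 mL/kg and depends on unstated placement for weights the bands omit

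*Protocol article*

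**What the plan says.** The footnote to Table 2 (protocol article, Blood sampling) sets the limit: "The maximum blood volume that can be taken for research over a 30-day period is 5% of a patients total blood volume (TBV". It then gives the conversion: "The TBV of a child is around 75–80 mL/kg".

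The table has four weight bands with printed 30-day maxima: 10–18 kg (40–72 mL), 19–29 kg (76–116 mL), 30–40 kg (120–160 mL) and >40 kg (>160 mL). In every band 2 mL is drawn on "Days 2, 4, 6, 8, 9, 11, 13". A larger volume of 3.25, 7.75, 13.25 or 18.25 mL, according to band, is drawn on "Days 1, 3, 5, 7, 10, 12, 14, 28, months 3, 6, 12, 24".

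The Blood sampling text says that the larger volumes "will be dependent on their weight (table 2", so weight selects the row. The table nevertheless prints an age range beside each band (1–5, 5–7, 8–12 and 12–15 years), and ages 5 and 12 each appear twice.

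The paediatric inclusion criterion reads "Patients aged 1–15 years admitted with a ≥20% TBSA burn" and states no minimum weight. Data collection and patient outcomes gives the later visit windows as "day 28 (±3 days) and months 3, 6, 12 and 24 (±2 weeks".

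**The concern.** The cap is the study's own safety limit on research blood in children with burns of at least 20% TBSA. Such a limit should hold for every eligible child over the whole range of blood volume that the same footnote accepts. Two features of the table put that in doubt.

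- The printed maxima appear to rest on the upper end of the 75–80 mL/kg range only, which is the end that allows the most blood.
- The draw volumes appear to have been set so that the schedule uses up the maximum at the lightest weight in each band. With no margin there, the choice of mL/kg and the row given to a child between or below the bands decide whether the cap is met.

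**Working it through.** **Inputs (all from Table 2 and its footnote).** Cap: 5% of TBV per 30 days. TBV: 75–80 mL/kg. Draws within 30 days: 7 of 2 mL (days 2, 4, 6, 8, 9, 11, 13) and 8 larger ones (days 1, 3, 5, 7, 10, 12, 14, 28). The draws at months 3 to 24 fall outside the period.

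**Step 1: reproduce the printed maxima.** Cap = 0.05 × TBV per kg × weight. At 80 mL/kg this is 4 mL/kg:
- 10 and 18 kg: 40 and 72 mL
- 19 and 29 kg: 76 and 116 mL
- 30 and 40 kg: 120 and 160 mL
- above 40 kg: more than 160 mL

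All match the table, so 80 mL/kg is the basis used.

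**Step 2: scheduled 30-day total** = 7 × 2 + 8 × larger draw:
- 14 + 8 × 3.25 = 40 mL
- 14 + 8 × 7.75 = 76 mL
- 14 + 8 × 13.25 = 120 mL
- 14 + 8 × 18.25 = 160 mL

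Each equals the 80 mL/kg cap at the lower edge of its band, exactly 5.00% of TBV. Above that edge the cap rises and the total does not, so at 80 mL/kg no child in a printed band exceeds the cap.

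**Step 3: the same totals at 75 mL/kg** (cap 3.75 mL/kg). The weight up to which the total exceeds the cap is total / 3.75.

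| Band | Total (mL) | Cap at lower edge (mL) | Excess (mL) | Over the cap for |
|---|---|---|---|---|
| 10–18 kg | 40 | 37.5 | 2.5 | 10 to below 10.67 kg |
| 19–29 kg | 76 | 71.25 | 4.75 | 19 to below 20.27 kg |
| 30–40 kg | 120 | 112.5 | 7.5 | 30 to below 32.0 kg |
| >40 kg | 160 | 150 (limiting value) | 10 | just above 40 to below 42.67 kg |

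At the edge the share of TBV is 40 / (75 × 10) = 5.33%, and it is the same in every band. The total is 40 / 37.5 = 1.067 times the cap, or 6.7% over. In the last band 40 kg is only a limit: a child of exactly 40 kg belongs to the 30–40 kg row (120 mL against 150 mL at 75 mL/kg, within the cap).

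**Step 4: weights with no row, taken at 80 mL/kg.**
- 18.5 kg: cap 4 × 18.5 = 74 mL. Higher row 76 mL (5.14% of TBV); lower row 40 mL (2.70%).
- 29.5 kg: cap 4 × 29.5 = 118 mL. Higher row 120 mL (5.08%); lower row 76 mL (3.22%).
- 9 kg: cap 4 × 9 = 36 mL. First-row volumes would total 40 mL (5.56%).

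The weights 18.5, 29.5 and 9 kg are illustrations. The same holds throughout each gap, because 76 mL exceeds 4 mL/kg at any weight below 19 kg, 120 mL at any weight below 30 kg, and 40 mL at any weight below 10 kg.

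**The case against.** The strongest reply is that the printed maxima are the operative limits and the schedule respects them for every child in a printed band. On this view the 75–80 mL/kg figure is an approximation in a footnote, and the conflict arises only at its lower end. This stands in part. It rules out saying that the schedule breaks the cap in general. It does not remove the inconsistency, because the footnote defines the cap as a share of TBV and itself accepts 75 mL/kg.

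Second, the excess is small and needs nearly complete sampling. Leaving out one larger draw brings every row under the 75 mL/kg cap at the lower edge: 36.75 against 37.5, 68.25 against 71.25, 106.75 against 112.5, and 141.75 against 150 mL. A day 28 sample taken on day 31, which the ±3 day window permits, may fall outside a 30-day period starting on day 1. Both points stand. A schedule should still meet its cap when it is followed as planned.

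Third, the gaps do not by themselves produce an excess. Nothing says that an 18.5 kg child goes to the higher row or that a 9 kg child receives first-row volumes. This also stands: the gaps can lead to an excess, depending on placement.

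Fourth, Figure 2 is not reproduced in the text at hand and the article condenses a fuller protocol, so a rule for in-between or lighter children may exist there. That cannot be checked. It bears on the gaps and the missing row, but it does not alter what Table 2 and its footnote state about the printed bands.

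A reader might also infer that the overlapping ages cause draws above the cap, for instance when a 12-year-old of 35 kg (an assumed weight) is placed by age in the last row: 160 against 140 mL at 80 mL/kg. The document does not support this. It makes weight the deciding variable, and by weight that child is in the 30–40 kg row, at 120 against 140 mL. The age labels are a secondary ambiguity only.

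**Conclusion.** The point holds as an inconsistency within Table 2. The maxima and draw volumes rest on 80 mL/kg, while the footnote allows 75–80 mL/kg, and the schedule leaves no margin at the lower edge of any band. At 75 mL/kg, correctly classified children at or just above each lower edge reach up to about 5.33% of TBV, an excess of 2.5 to 10 mL depending on the band. This assumes that all 15 draws are taken in full within 30 days. The excess shrinks to nothing as TBV approaches 80 mL/kg or as weight reaches the upper end of each strip in the working.

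For weights of 18–19 kg and 29–30 kg the cap can be exceeded even at 80 mL/kg, but only if the child is placed upward. For eligible children under 10 kg the table offers no row, and it would be exceeded if first-row volumes were applied.

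The tempting stronger reading, that the schedule exceeds the study's limit for children at large, is not supported. The excess is modest and confined to narrow weight strips, and it does not touch the endpoint, sample size or analysis. It is worth correcting because the figure is a patient safety limit and the conflict recurs in all four rows.

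**What to change.** The sponsor should reconcile Table 2's draw volumes, weight bands and mL/kg basis with the footnote's 5% limit, so that the limit demonstrably holds over the stated 75–80 mL/kg range and for every eligible weight, including those under 10 kg and those between the printed bands. The age labels should be made consistent with the statement that weight sets the volume. If Figure 2 or the full protocol already deals with these weights, the table should say so. Which volumes, bands or placement rule apply is for the sponsor and the clinical team, and none is proposed here.

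The cost is a table and footnote correction by amendment. If the reconciliation changes any draw volume, the laboratory's sample needs at those time points would have to be checked. The sample size and statistical analysis are unaffected.
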